### Plans to promote participant retention and complete follow-up

Home visits are offered for data collection to facilitate women’s participation in research assessments, although visits can take place elsewhere if preferred by the participant. Visits are flexibly arranged for a date and time of convenience for the participant. At the end of each visit, the appointment for the next visit is scheduled if possible. Participants are sent reminders about scheduled visits at 1 month, 1 week and 1 day before the scheduled date and time. We attempt to collect data in a 2-week window on either side of the follow-up due date, that is, date ±2 weeks, but allow flexibility outside of this window when women are actively engaging with the research team to arrange the visit. Participants’ preferred methods of contact are documented and prioritised. Three contact attempts using different methods, for example, text, phone, email, are made to all women to confirm scheduled visits and following non-attendance to reschedule. Women who are unable to complete a visit with the researcher at 6 months are sent a link to complete the questionnaire (via Qualtrics email link). As a last resort, when all attempts to arrange a face-to-face visit at 12 (primary endpoint) and 24 months are unsuccessful, participants are asked to provide self-reported weight and complete a questionnaire (via Qualtrics email link). Participants are sent a £25 voucher at each trial time point (0, 6, 12 and 24 months; £100 maximum over 24 months) as a token of appreciation for the time committed to completing trial assessments. Participants lost to follow-up at one trial time point but who have not withdrawn are invited to attend future visits.

To maximise data completeness, site researchers follow-up on any non-returned questionnaires and check all received data forms/e-forms to document data queries (eg, missing data, invalid ranges) and any attempts made to resolve them, for example, clarify responses with the participant, using a data query log.

### Data management

The hard copy of the CRF which records data at each time point including weight is the source data and requires sign-off by the completing researcher. For questionnaires, the hard copy or electronic record is considered the source data depending on mode of completion.

The Northern Ireland Clinical Trials Unit (NICTU) is responsible for developing and managing trial databases on validated and secure systems that back-up data, maintain audit trails of data changes and only allow password-protected access to designated trained team members. Screening and CRF data are entered into trial databases by site researchers and a 10% random quality control check of data completed by a different researcher. For Consolidated Standards of Reporting Trials (CONSORT) reporting, screening data includes anonymised summary information for women who do not proceed to randomisation. Paper questionnaires are scanned at site then the original posted to NICTU for data entry directly into the trial database.

Entered data are processed as per the trial-specific data management plan. Data queries are generated electronically by NICTU and site staff are required to respond to clarify data, provide missing information or make relevant amendments within the trial databases.

Online questionnaire completion is stored by the Qualtrics system on EU-based servers compliant with General Data Protection Regulation (GDPR) and exported by the Trial Manager for merging with the NICTU questionnaire database by the Trial Statistician (CC). Following completion of data collection, data are permanently deleted from Qualtrics.

Qualitative interview transcripts are anonymised and checked for accuracy against the audio recordings, then the recordings deleted.

A minimal amount of personal information (participant’s first name, mobile phone number and weeks postpartum at baseline) is entered into the randomisation system to allow delivery of text messages according to group allocation. Only designated trained team members have password-protected access to the randomisation system.

Text message engagement data are downloaded from the LSHTM system at the end of the intervention period in the form of all messages sent to and replies received from participants.

At the trial end, sites and NICTU send original source documentation (hard copy or electronic) along with consent forms and contact details for individuals who provided consent to be contacted about follow-up to this trial/future-related research/future data linkage to routinely collected health records, to QUB for archiving in accordance with the Sponsor’s requirements (10 years after end of trial/publication). The CI will conduct periodic reviews (every 5 years) to ensure the necessity of data retention. Any other documents containing personal data are confidentially destroyed. Sites are responsible for archiving general site files accumulated during the day-to-day operation of the trial.

### Data protection and confidentiality

All data are collected, stored and handled in accordance with the QUB Research Management Policy (2015), GDPR and any future relevant data protection legislation and all trial team members must be compliant with these regulations. Detailed description of the trial data processing is documented in a Data Privacy Impact Assessment and in the privacy notice given to women expressing an interest in the trial.

Participants are allocated a unique five-digit participant identifier at randomisation which is used on all data collection forms/files to allow identification of data for each participant, with the key for unlocking pseudonymised data held by site teams in password-protected files. Hard copies of forms are securely stored in locked filing cabinets in locked offices in buildings requiring keypad access and which are alarmed outside normal working hours. Consent and contact details forms, containing identifiable information, are stored separately from other data (CRFs and questionnaires) and will not be kept for longer than is required. All electronic forms or data files are held on password-protected systems that are routinely backed up and are only accessible using username, password and/or multifactor authentication. Third-party transcription providers sign a confidentiality agreement detailing data handling requirements. Any file transfer between QUB and other parties (sites/transcription provider) is done, subject to relevant data sharing agreements, via secure and encrypted file transfer systems (eg, QUB Dropoff). Participants will not be identifiable from any published trial report.

Data collected from women expressing an interest in trial participation but who are not recruited will be confidentially shredded/deleted.

### Access to data

Access to trial records and source data can be granted to the authorised sponsor (or delegate), REC, host institution and regulatory authority representatives for trial-related monitoring, audits and inspections, as per participant consent.

Only employed trial team members have access to the personal/sensitive data of participants and data are shared with those responsible for the healthcare of the participants only when health concerns are raised, for example, Edinburgh Postnatal Depression Scale (EPDS) score of 9 or greater.^30^

The trial manager, statistician and health economist will have access to the anonymised dataset at the trial end, to permit analysis.

The CI will manage access rights to the trial data set, in collaboration with the sponsor, and formal requests for data access need to be made in writing to the CI. The trial will comply with the good practice principles for sharing individual participant data from publicly funded trials and data sharing will be undertaken in accordance with the required regulatory requirements. Any transfer of data to other institutions will be governed by a data access agreement and will be in the form of an anonymised dataset. In the event of publications arising from further data analyses, those responsible will need to provide the CI with a copy of any intended manuscript for approval prior to submission.

### Statistics and analysis

Aligned with best practice and following appropriate reporting guidelines, a statistical analysis plan,^63^ health economics analysis plan^64 65^ and process evaluation analysis plan are written and approved by the PMT and TSC prior to analysis. Trial results will be reported in accordance with the CONSORT guidelines, with the flow of participants summarised in a CONSORT flow diagram (http://www.consort-statement.org/) and tables of summary baseline characteristics presented by total recruited sample and 12-month completers.

### Primary outcome analysis

Weight change (kg) at 12 months will be compared on an intention-to-treat basis (ie, all participants as randomised and regardless of whether or not they engaged with the text messages) between the intervention and active control groups, adjusted for weight at baseline, site, recruitment method (community vs NHS) and ethnicity. The adjusted difference in means between the groups, corresponding 95% confidence intervals and p value will be reported. A complete-case approach will be used. Sensitivity analysis assessing the impact on the primary outcome analysis will be conducted to (1) include participant self-reported weight, only where researcher-measured weight is not available and (2) use last observation carried forward, multiple imputation to impute missing outcome values and delta methods to explore the impact of worse or better outcomes in the individuals with missing data.

The independent TSC in conjunction with NIHR will decide if the trial should progress to stage 3 (24-month follow-up and stakeholder engagement) based on assessment of the 12-month primary outcome data and any other core outcome data required to make a fully informed decision at 12 months (end of intervention). If the trial proceeds, a further analysis of weight change (kg) will be conducted at 24 months. Despite the sequential nature of this comparison, we do not intend to change the significance level because this test will be a secondary analysis.

All testing will be done at the two-sided 5% significance level. All analyses will be conducted using STATA version 16 software (Statcorp).

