Postpartum weight management interventions combining dietary and activity behaviour change have moderate positive influence on maternal weight^10 14^ and those including self-regulatory BCTs are likely to be more successful.^8 10^ The postpartum period could be an ideal time to intervene to shape new health behaviours as women may be motivated and receptive to health information.^41^ However, women highlight a need for additional weight management support during the postpartum period as little is currently provided.^42^

The present trial allows women to take part up to 24 months post partum. Qualitative evidence suggests that every woman’s postpartum journey is different^19–23^ and the optimal time to engage women in postpartum weight management is currently unknown.^9 11^ Allowing this extended inclusion window accommodates different maternal weight trajectories across this time.^43 44^ Furthermore, women may prepare for another pregnancy during this period so there is potential to support better health for subsequent pregnancies.^7^

Mobile phone usage and ownership are widespread (95% of UK households) among all sectors of society, irrespective of socioeconomic status (SES).^31^ Text messaging is a simple communication mode that does not require smartphone or tablet technology, unlike web-based interventions or apps. This supports health equity through high reach potential at a low cost, making it conducive with scale-up and implementation, unlike some weight loss interventions which can be resource intensive and expensive^45^ and can exacerbate health inequalities.^46 47^ A text messaging intervention can be delivered flexibly and on a sustained basis, can be reactive and proactive, and does not necessarily rely on participant initiation.^30 48^ Using the real-time advantages offered by mobile technologies to deliver behavioural weight management support to postpartum women has the potential to encourage behaviours that may improve maternal health in both the short and long term.^49^ Trial results are relevant for other population groups given the possible advantages of this weight management approach. The NHS aims to embrace the potential of digital strategies for improving UK health^50^ and text message interventions could complement any weight management support currently delivered across the NHS, to help ease the current burden on an overstretched service.

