Habit behaviour	Self-report behavioural automaticity index^83^	✓	✓	✓	✓
Self-regulation of eating behaviour	Self-regulation of eating behaviour questionnaire^84^	✓	✓	✓	✓
Weight self-monitoring	Trial-specific questions	✓	✓	✓	✓
Diet and exercise monitoring	Trial-specific questions	✓	✓	✓	✓
Goal-setting for diet and exercise	Trial-specific questions	✓	✓	✓	✓
Weight loss motivation	Motivation for weight loss scale^85^	✓	✓	✓	✓
Taking part in other weight loss programme	Trial-specific questions	✓	✓	✓	✓
Social support	Social support for eating and exercise^86^ plus general social support (Born in Bradford trial-specific questions)	✓	✓	✓	✓
Self-esteem	Rosenberg Self-Esteem Scale^87^	✓	✓	✓	✓

*Recorded in case report form.

†Date of birth, where they heard about the trial, NHS number, ethnicity, income, postcode, employment, education, relationship status, weeks postpartum at trial entry, parity, medical information (disability status, medication use), infant feeding, weight history, smoking status, alcohol intake, technology usage.

‡Recorded in participant self-reported questionnaires.

MaMB/MaMC, Me and My Baby/Me and My Child; NHS, National Health Service.

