### Secondary outcome analysis

Similar analyses will be conducted for secondary continuous outcomes and for secondary analyses of outcomes at other time points. Binary outcomes will be analysed using logistic regression, comparing the intervention and active control groups while adjusting for site, recruitment method and ethnicity. Adjusted odds ratios with 95% confidence intervals and corresponding p values will be reported. Secondary analyses will be considered exploratory and hence the p values will not be altered to control for multiple testing. The focus of all secondary analyses will be on estimating the difference between groups with 95% confidence intervals rather than hypothesis testing.

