### Methods for additional analyses (eg, subgroup analyses)

To understand any differential effects of the intervention, subgroup analyses will be conducted stratifying by prespecified variables including site, SES, ethnicity, recruitment method, weeks postpartum (at baseline), BMI (at baseline) and parity. Interaction tests will be conducted, separately, by including interaction terms within regression models. The significance level for subgroup analyses will not be reduced but will be interpreted cautiously. As recommended, all subgroup analyses will be reported.^66^

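### The primary model leaves out weeks post partum, and the logistic models leave out baseline weight or the baseline outcome, although all are collected: a small efficiency loss and an unexplained inconsistency, not a bias

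*Protocol article*

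**What the plan says.** All references are to the Protocol article.

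- **Primary outcome analysis.** Weight change at 12 months is compared between groups, "adjusted for weight at baseline, site, recruitment method (community vs NHS) and ethnicity". The list is explicit and does not contain weeks post partum.
- **Secondary outcome analysis, continuous outcomes.** "Similar analyses will be conducted for secondary continuous outcomes and for secondary analyses of outcomes at other time points". This carries over the primary approach, including adjustment for baseline.
- **Secondary outcome analysis, binary outcomes.** Logistic regression, "comparing the intervention and active control groups while adjusting for site, recruitment method and ethnicity". Neither baseline weight nor a baseline value of the outcome is listed. Secondary analyses are declared exploratory, with the emphasis on estimation.
- **Rationale.** On recruiting up to 24 months after birth: "Allowing this extended inclusion window accommodates different maternal weight trajectories across this time".
- **Outcomes, Table 1 and its footnote.** Weight and infant feeding are measured at month 0. The demographic items include "weeks postpartum at trial entry, parity, medical information".
- **Methods for additional analyses.** The prespecified subgroup variables include "recruitment method, weeks postpartum (at baseline), BMI (at baseline) and parity", each with an interaction test.
- **Sequence generation.** Randomisation is stratified by site only.

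**The concern.** Women enter between 6 weeks and 24 months after birth, and the protocol itself expects weight to follow different courses over that window. Time since birth is therefore a natural candidate predictor of 12-month weight change. The plan does not confine adjustment to stratification factors, since it also includes recruitment method and ethnicity, so its own logic does not explain the absence of weeks post partum. The variable appears only in subgroup models, not in the model that gives the primary estimate.

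The binary models raise a clearer question. Gain of more than 5 kg is a dichotomised form of the weight change that the primary model analyses with baseline weight as a covariate. The same construct is thus analysed with two covariate sets, and the shorter one drops a value measured on every woman at entry. Infant feeding also has a month-0 measurement, so the same point arises if it is analysed as a binary outcome.

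At stake is some power and interval width on the primary outcome, some power on the binary outcomes, and consistency between the two kinds of model.

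**Working it through.** **1. The plan's own figures (Sample size calculation).** Inputs: difference 2 kg, SD 7.5 kg, two-sided 5%, 90% power.

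- n per arm = 2(z₀.₉₇₅ + z₀.₉₀)² × SD² / Δ² = 2 × (1.960 + 1.282)² × 56.25 / 4 = 295.6, so 296. The plan has 297 per arm (594).
- At 297 per arm, SE = 7.5 × √(2/297) = 0.6155 kg. Power = Φ(2/0.6155 − 1.96) = 90.1%.
- Randomised: 119/0.70 = 170 and 119/0.63 = 188.9, so 189. Then 3 × 170 + 2 × 189 = 888.

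All stated figures reproduce, and none takes credit for covariate adjustment.

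**2. Adding weeks post partum to the primary model.** Let R² be the extra share of variance it explains beyond the listed covariates, with 7.5 kg taken as the SD before it is added. The document gives no value, so 0 to 10% is an assumption. Residual SD = 7.5 × √(1 − R²).

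| Assumed extra R² | Residual SD (kg) | SE (kg) | 95% CI half-width (kg) | Power at 297 per arm | n per arm for 90% |
|---|---|---|---|---|---|
| 0% | 7.500 | 0.6155 | 1.21 | 90.1% | 296 |
| 2% | 7.425 | 0.6093 | 1.19 | 90.7% | 290 |
| 5% | 7.310 | 0.5999 | 1.18 | 91.5% | 281 |
| 10% | 7.115 | 0.5839 | 1.14 | 92.9% | 266 |

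**3. What these R² values imply.** Assume entry is uniform over weeks 6 to 104, so SD = 98/√12 = 28.3 weeks.

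- Slope 0.02 kg per week: (0.02 × 28.3 / 7.5)² = 0.6%.
- Slope 0.05 kg per week: (0.05 × 28.3 / 7.5)² = 3.6%, a difference of 0.05 × 98 = 4.9 kg in 12-month change between the earliest and latest entrants.
- R² of 10% needs √0.10 × 7.5 / 28.3 = 0.084 kg per week, or 8.2 kg across the window.

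The top of the range therefore supposes a strong relation.

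**4. Chance imbalance.** The between-arm difference in mean weeks has SD 28.3 × √(2/297) = 2.3 weeks. At a slope of 0.05 kg per week, its 95% range moves the estimate by 1.96 × 2.3 × 0.05 = ±0.23 kg. This lies inside the ±1.21 kg interval and does not add to it.

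**5. Logistic models.** Simulation with 594 women, 2000 runs per setting, an assumed 20% event rate in the control arm, an assumed conditional log odds ratio of −0.6 for treatment, and one standardised baseline covariate. The unadjusted model contains treatment only.

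| Covariate log OR per SD (assumed) | Power without it | Power with it | Mean log OR without | Mean log OR with |
|---|---|---|---|---|
| 0.3 | 74.1% | 74.5% | −0.592 | −0.601 |
| 0.7 | 69.9% | 73.9% | −0.568 | −0.604 |
| 1.5 | 54.1% | 66.4% | −0.465 | −0.609 |

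With no treatment effect, rejection ran from 3.9% to 6.5%, and the two models differed by at most 0.55 points in any setting. The gain is negligible for a weak predictor and about 12 points for a very strong one. It comes with an odds ratio that moves away from 1, not with a smaller standard error.

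**The case against.** The case for leaving the plan alone is substantial, and most of it stands.

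- **The primary model is sound.** It includes baseline weight and the only stratification factor. A reader might infer that omitting weeks post partum biases the result or inflates type I error. It does neither under randomisation.
- **Chance imbalance.** A reader might infer that imbalance in time since birth goes uncorrected. It is not conditioned on, but the standard error already covers it.
- **Complete cases.** About a third of women are expected to be lost (888 − 594 = 294), many through pregnancy, and time since birth may predict both pregnancy and weight. A reader might infer a biased contrast. That would require the missingness process to differ by arm or the effect to vary with timing. The document shows neither, and it plans multiple imputation and delta-method sensitivity analyses.
- **Scope of the binary omission.** It would be wrong to say that these models contain no baseline information: site, recruitment method and ethnicity are baseline factors. Gain of more than 5 kg has no baseline value of its own, so only baseline weight could be added. It is the only secondary outcome stated as a proportion. Diet, activity and infant feeding are not said to be binary.
- **Low stakes.** Secondary analyses are exploratory, and a separate SAP, not shown here, may say more.

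The objection does not remove two facts. Both covariate lists are written out in the protocol, so the omissions are stated choices, not silence. And no reason is given for dropping baseline weight from a dichotomised weight change when the continuous version adjusts for it.

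**Conclusion.** The point holds as a minor one. The primary model omits weeks post partum, and the logistic models omit baseline weight or the baseline value of the outcome, although these are collected at month 0. The planned analyses are valid and the power claim of over 90% is correct.

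On the primary outcome the possible gain runs from nothing to about 2.8 percentage points of power (90.1% to 92.9%) and 0.06 kg of confidence interval half-width (1.21 to 1.14 kg before rounding, that is 1.206 to 1.144). This rests wholly on the assumed extra R² of 0 to 10%. For binary outcomes the gain depends on how predictive the baseline value is, which the document also does not give, and the simulated figures rest on an assumed event rate and effect.

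The inconsistency between the continuous and binary models for weight is the firmest part, because it can be read directly from the text without any assumption.

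**What to change.** Before unblinding for the 12-month analysis, state in the analysis plan that:

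1. the logistic model for gain of more than 5 kg also adjusts for baseline weight;
2. any other outcome analysed as binary adjusts for its baseline value where one was measured;
3. weeks post partum at entry is a continuous covariate in the primary and secondary models, with its functional form prespecified;
4. optionally, a standardised risk difference is reported beside each odds ratio.

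No new data are needed. The cost is a change of wording, a few degrees of freedom, and an odds ratio conditional on more covariates and so not directly comparable with one from the shorter list. Item 4 offsets that last cost. If gain of more than 5 kg proves much rarer than the 20% assumed above (594 × 0.20, about 119 events), the number of terms in the logistic model should be checked against the pooled event count before allocation is revealed.

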### Eligibility criteria

Women (in accordance with the NICE Postnatal care guideline NG1941, the term ‘woman’ used in this trial includes people who do not identify as women but who are pregnant or have given birth) are eligible to participate in the trial if they are aged over 18 years, have a BMI of ≥25 kg/m^2^ and have had a baby within the last 2 years.

Women are excluded if their baby is less than 6 weeks old, if they have no access to a mobile phone to allow them to receive personal text messages or if they have insufficient English language to understand short written messages, if they have had or plan to have any type of bariatric surgery, if they report having ever received a diagnosis of anorexia nervosa or bulimia from a doctor, or, if they are on a specialist diet and receiving dietetic care. Women are excluded if they are participating in any other weight management research study/programme currently or in the previous 3 months. Women are not eligible if they are pregnant and any consented participant becoming pregnant during the trial is excluded, as the intervention has not been designed for use in pregnancy.

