### Informed consent and withdrawal

For women meeting the eligibility criteria and willing to proceed with trial participation, a baseline researcher visit is arranged. Home visits are the primary approach to data collection, with women also offered the option of attending another venue if preferred (University building, community venue or their workplace).

Research staff, trained in Good Clinical Practice (GCP) guidelines, obtain written informed consent prior to collecting baseline data. At the baseline visit, women are offered the opportunity to ask further questions and confidentiality of data is explained. Informed consent is then taken. Women are reminded that they have the freedom to choose whether to take part or not. If willing to proceed, women are asked to initial and sign the trial consent form, with optional consent to be invited for telephone interview participation at 6 and 12 months. During the 6-month and 12-month trial visits, women providing this optional consent at baseline are asked if they are still happy to be contacted to take part in a telephone interview. Participants completing telephone interviews are asked to provide their verbal consent for audio recording and for anonymised quotations to be used in trial publications before commencing interviews.

Once consented, participants are advised that they can withdraw from the trial at any time and without giving a reason, should they wish. Withdrawals are documented in the case report form (CRF) along with any reason given for withdrawing. Participants excluded due to pregnancy are given the option to continue receiving the text messages. Anyone choosing this option needs to complete and return a pregnancy form to acknowledge that the messages have not been designed for pregnancy but may be useful after pregnancy. Data collected up to the point of withdrawal are retained for analysis unless the participant specifies otherwise.

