### Statistical methods to handle protocol non-adherence and missing data

The primary analysis of weight change (kg) at 12 months will be on an intention-to-treat basis.

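### The primary analysis is labelled intention-to-treat of all randomised women, but it is a complete-case analysis that is expected to leave out a third of them and does not use their 6-month weights

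*Protocol article*

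**What the plan says.** All references are to the protocol article.

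- *Primary outcome analysis* defines the intention-to-treat basis as "all participants as randomised and regardless of whether or not they engaged with the text messages". It then says "A complete-case approach will be used". The comparison is "adjusted for weight at baseline, site, recruitment method (community vs NHS) and ethnicity"; 6-month weight is not in that list.
- The same section plans sensitivity analyses. One adds self-reported weight where no measured weight exists. The other will "use last observation carried forward, multiple imputation to impute missing outcome values and delta methods", the last of these covering better or worse outcomes in women with missing data.
- *Statistical methods to handle protocol non-adherence and missing data* contains one sentence: "The primary analysis of weight change (kg) at 12 months will be on an intention-to-treat basis".
- *Eligibility criteria* states that "any consented participant becoming pregnant during the trial is excluded". *Relevant concomitant care* explains that the primary outcome cannot be collected in pregnancy.
- *Sample size calculation* plans for 594 completers out of 888 randomised.
- Table 1 schedules measured weight at 0, 6, 12 and 24 months. *Informed consent and withdrawal* adds: "Data collected up to the point of withdrawal are retained for analysis unless the participant specifies otherwise".

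**The concern.** Once outcomes are missing, an analysis cannot both include all women as randomised and be restricted to complete cases. The protocol expects many missing outcomes and says so in its sample size. A reader of the trial report would see an intention-to-treat label on a result that describes women who were not pregnant and were weighed at 12 months.

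Two things are at stake. The first is validity: a woman weighed at 6 months and absent at 12 contributes nothing to the primary estimate, although her early weight change carries information about the missing value. If the women who leave after month 6 are selected on that early change, and the selection differs between arms, the complete-case difference shifts. The second is precision, because collected data are set aside. The 12-month result also feeds the decision on whether to proceed to the 24-month stage.

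**Working it through.** **1. Reproducing the plan's figures.** Inputs from *Sample size calculation*: difference 2 kg, SD 7.5 kg, 297 per group, two-sided 5%.

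- Power = Φ(2 / (7.5 × √(2/297)) − 1.96) = Φ(3.25 − 1.96) = 0.901 (0.900 by t-test). This agrees with the stated figure of over 90%.
- Site sizes: 119/(1 − 0.30) = 170 and 119/(1 − 0.37) = 188.9, rounded up to 189. Total: 3 × 170 + 2 × 189 = 888. Completers: 5 × 119 = 595, against 594 required.

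The sample size arithmetic is correct and is not the fault.

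**2. The share left out.**

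- From the totals: 888 − 594 = 294, and 294/888 = 33.1%, or 147 per group.
- Expected pregnancies: 510 × 0.15 + 378 × 0.22 = 76.5 + 83.2 = 159.7, or 18.0% of 888.
- Expected loss to follow-up: 888 × 0.15 = 133.2, or 15.0%.
- Together: 292.9/888 = 33.0%.

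These are anticipated rates. The pregnancy part follows from the protocol's own exclusion rule; the rest is expected loss.

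**3. Possible bias (illustration on assumed inputs).** The documents give neither the correlation between 6- and 12-month weight change nor the timing of loss. Assumed: 444 per arm, SD 7.5, true effect −2.0 kg, correlation 0.75, half of the loss after month 6. The odds ratio (OR) is for late loss per SD of 6-month weight gain. Ranges reflect small differences in how the simulation is coded.

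| Late loss depends on 6-month gain | Complete-case estimate (kg) | Shift from −2.0 (kg) |
|---|---|---|
| OR 1.65, intervention arm only | −2.53 to −2.59 | 0.53 to 0.59 |
| OR 1.65, control arm only | −1.42 to −1.48 | 0.52 to 0.58 |
| OR 1.3, intervention arm only | −2.28 | 0.28 |
| OR 1.65 in one arm, 1.3 in the other | −2.23 | 0.23 |
| One arm only, pregnancy unrelated to weight | −2.29 or −1.73 | 0.29 or 0.27 |
| OR 1.65 in both arms | −2.01 | about 0 |

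In the one-arm scenarios with OR 1.65, an analysis using the 6-month weights returned −1.99 to −2.02.

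**4. Precision (also on assumed inputs).** Let m be the number of non-completers per arm with a 6-month weight and ρ the 6-to-12-month correlation. Then n_eff = 297 / (1 − ρ² × m/(297 + m)).

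- Low end: 25% of 147, m = 36.75, ρ = 0.5. n_eff = 297/(1 − 0.25 × 36.75/333.75) = 305; power 91%.
- High end: 75% of 147, m = 110.25, ρ = 0.85. n_eff = 297/(1 − 0.7225 × 110.25/407.25) = 369; power 95%.

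The gain is from 90% to about 91–95%.

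**The case against.** The sponsor has a good deal to say in reply.

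- *The label is partly met.* Women are compared by allocated arm regardless of engagement, and those who stop messages stay in the trial. This stands. What is not met is the inclusion of everyone randomised.
- *Missing data are not ignored.* Multiple imputation, delta methods and a self-reported-weight analysis are prespecified, and the variables in the imputation model belong in the analysis plan. This stands too; the remaining question is which analysis supplies the headline estimate and p value. Last observation carried forward adds little, since it assumes no change after the last weight and zero change where only baseline exists.
- *Bias is not shown.* A reader might infer that a complete-case difference is unbiased only if missingness is unrelated to weight course, or that this trial's estimate will be biased by half a kilogram. The documents support neither. The same dependence in both arms leaves the difference almost unchanged, and the largest shifts need strong dependence in one arm and none in the other. The pilot reported high retention and no differential attrition, and the active control was chosen to protect retention. Equal drop-out rates can still hide different reasons for leaving, so a risk remains.
- *6-month data are incomplete.* Women who miss that visit receive only a questionnaire link, and self-reported weight is collected only at 12 and 24 months. This limits the gain.
- *Pregnancy is not solved by a model.* This is correct: how those women enter the effect is a choice about the question being asked, and 6-month weights alone do not settle it.

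**Conclusion.** The point holds as a mismatch between label and analysis set, together with an avoidable loss of information. The protocol's own figures put about 294 of 888 women (33%) outside an analysis described as covering all of them, and the stated model does not use their measured 6-month weights.

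The bias is a possibility conditional on arm-specific dependence of late loss on early weight change. Its illustrated size, from about zero to about 0.6 kg against a 2 kg design difference, rests on an assumed correlation of 0.75, an assumed half of the loss after month 6 and assumed odds ratios. The power gain likewise rests on assumed correlations and 6-month availability. This should be fixed before the 12-month analysis is unblinded, but it does not invalidate the design or the sample size.

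**What to change.** 1. Make the primary analysis a likelihood-based repeated-measures model of baseline, 6- and 12-month weight, by randomised arm, with the covariates already listed. Multiple imputation that includes 6-month weight is an acceptable alternative.
2. Keep the complete-case ANCOVA as a sensitivity analysis and call it that. Do not rely on last observation carried forward.
3. State that 12-month weights missing because of pregnancy are handled under a hypothetical estimand: the effect had the woman not become pregnant.
4. Run the planned delta analyses separately for pregnancy and for other loss.
5. Use the missing-data section to describe this handling in place of repeating the intention-to-treat label.

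The cost is a change of wording in the protocol and analysis plan and a few lines of Stata; no new data are needed. The primary model becomes slightly more complex and still rests on a missing-at-random assumption, and some non-completers will have no 6-month weight to contribute.
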